### Data collection

Prior to inclusion in the study, each participant will undergo a simple ergometry test to determine their maximum heart rate (MHR), observe their behavior at maximum effort, and rule out conditions that contraindicate exercise. Besides, the rehabilitation physician will perform a nutritional assessment using bioimpedance analysis and a morphological assessment of the quadriceps and abdominal fat using ultrasonography. Patients will be weighed every week to monitor their evolution and rule out possible adverse effects of training. At the end of the program, ergometry, blood analysis, and the rest of the tests described below will be repeated.

#### Status and timeline of the study.

Currently, patients are still being recruited for the study. This is planned to be completed on December 31, 2025. Data collection is expected to be concluded by March 31, 2026, and we expect to have the results ready for publication in the second quarter of 2026.

#### Data management plan.

To ensure the privacy and confidentiality of participants, all clinical data collected in the study will be anonymized prior to analysis. Direct identifiers such as names, identification numbers, and specific dates will be removed, and indirect variables that could allow for the identification of subjects will be grouped and coded. The anonymization process will be carried out in accordance with current ethical and regulatory standards, ensuring that the data retained its validity for statistical analysis without compromising individual privacy. All physical documents (informed consent forms, data of the outcomes of the participants, etc.) will be stored in locked filing cabinets located in a secure area with restricted access. Electronic data will be entered into a secure, password-protected database designed specifically for the study. Only members of the research team listed in the protocol will be granted access to the data. The data that will support the findings of this study will not be openly available due to reasons of sensitivity and will be available from the corresponding author upon reasonable request. Data will be in controlled access data storage at University of Cadiz (Spain).

Participant data and variables will be gathered, as depicted in Figs 1 and 2.

**Fig 1 pone.0343947.g001:**
[figure not shown]
Schedule of enrolment and interventions.

**Fig 2 pone.0343947.g002:**
[figure not shown]
Schedule of assessments.

### Statistical analysis

Descriptive statistics will summarize each variable, reporting means ± standard deviations (SD) or medians (IQR) for continuous data and absolute and relative frequencies for categorical data to verify baseline comparability between groups. Exploratory data analysis (e.g., box-plots, z-scores) will screen for influential outliers; values deemed spurious will be winsorized or, when justified, excluded, and sensitivity analyses will confirm that their treatment does not alter the main findings.

A mixed-design analysis of variance (ANOVA) will be performed to assess differential changes between groups over time (group × time interaction). The primary analysis strategy will depend on the proportion of missing data: if the dropout rate is less than 5%, a complete case analysis will be conducted, as this threshold is generally considered to have a negligible impact on bias. However, if missing data exceeds 5%, an intent-to-treat approach will be implemented, using multiple imputation to handle missing values and ensure that all randomized participants are included in the final model, in accordance with clinical trial standards [42].

All analyses will be performed in IBM SPSS Statistics v.24 (IBM Corp., Armonk, NY, USA), significance level will be set at 5% with 95% confidence intervals; assumptions, model fit, and potential risks (e.g., heteroscedasticity or multicollinearity) will be routinely checked, and predefined contingency strategies (nonparametric alternatives or robust estimators) will be implemented when violations are detected.

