**Methods:**

72 patients diagnosed with AMI will be enrolled and randomly assigned to two groups. The control group will complete the usual CRP with the addition of IMT at 5% of the maximal inspiratory pressure (MIP) (sham load). The intervention group will perform the same CRP but will add an IMT program at 70% of MIP. Outcomes will be collected at baseline and post-intervention. The main outcome will be cardiorespiratory fitness (CF) measured in metabolic equivalent of task (MET), secondary outcomes will be MIP, maximal expiratory pressure, peripheral muscle strength, dyspnea, social support, anxiety, depression, coping with the disease, sexual dysfunction, quality of life (QoL), sleep quality, eating habits, and body composition. Descriptive statistics will summarize baseline data, and influential outliers will be managed via winsorization or exclusion, confirmed by sensitivity analyses. A mixed-design ANOVA will evaluate differential changes over time. Depending on attrition rates, missing data will be addressed using either complete case analysis (<5%) or multiple imputation with an intention-to-treat approach (>5%).

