#### Clinical outcomes.

Comorbidities will be recorded at baseline based on medically documented diagnoses of chronic conditions coexisting with primary health concerns. Before and after the intervention, the following assessments and evaluations will be performed.

To assess CF, simple ergometry will be performed following the clinical guidance by consensus of recommendations for clinical exercise tolerance testing according to The Professional Body for Cardiac Scientists [25], in which the maximum oxygen consumption (VO_2_max), duration of the test, and type of response will be measured. Ergometry, also known as a stress test, is a diagnostic technique that analyzes the response of the heart to exercise and quantifies the oxygen consumption of the individual performing the test. In this study, the exercise will be performed on a treadmill. The Bruce protocol, which progressively increases the speed of the treadmill and its inclination every 3 min, will be used. This procedure will be performed by a cardiologist in our unit. VO_2_max will be obtained in METS (a metabolic equivalent of task, 1 MET = 3.5 ml O_2_/kg/min). The time and type of response will be recorded. This may be clinically positive if the cardiologist appreciates the appearance of angina on exertion or is electrically positive if a horizontal or downward depression of the ST segment of 1 mm measured at 80 ms from the J point is present.

Left ventricular ejection fraction (LVEF) will be measured by a cardiologist using ultrasound, following the recommendations of the American Society of Echocardiography for use in clinical trials and in agreement with expert cardiologists [26].

The total number of sessions attended by each participant will be recorded at the end of the intervention period.

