#### Strength measurements.

A MicroRPM® digital portable manometer (Vyaire Medical GmbH, Hoechberg, Germany) will be used to measure the MIP and MEP. These assessments will be performed according to the recommendations of the American Thoracic Society (ATS) [27] and the European Respiratory Society (ERS) [28] and following the protocol of the Spanish Society of Pneumology and Thoracic Surgery (SEPAR) [29]. MIP will be reassessed midway through the program (at the end of week 4) to readjust the training load.

Perypheral musculature will be assessed as follows. Maximum static quadriceps muscle strength will be measured with the patient seated on a stretcher and the knee flexed at 90° using a Hogan Health Industries model MicroFet 2 handheld dynamometer. Hand grip strength will be measured using a Jamar^Tm^ approved hydraulic dynamometer. The isometric strength of the hand and forearm muscles will be assessed with the arm extended along the body by performing a contraction for at least 3 seconds. The three maneuvers will be performed at least 20 seconds apart. The highest value obtained will be considered.

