### Sample size calculation

The sample size was calculated to detect differences between groups in our main outcome, CF, measured by VO_2_max. According to the meta-analysis by Fabero-Garrido et al [16], people with ischemic heart disease who have undergone an IMT program have a mean difference of 2.18 ml O_2_/kg/min with respect to the control group, and we want to find a deviation of 1 MET (3.5 ml O_2_/kg/min). The calculations were performed using the statistical software G*Power 3.1, considering a confidence level of 95% and a power of 80% in all cases.

Based on the above, a sample size of 33 subjects per group (66 in total) was determined. In addition, to minimize the impact of possible dropouts, the total sample was increased by 10% to 72 patients, which will lead to the final inclusion of 36 patients in each group.

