As limitations, we believe that the high number of questionnaires that the patients will have to answer could exhaust some of the participants and it could happen that they would not answer all of them. To try to avoid this, at the beginning of the intervention, the CRU nurse will explain to participants the importance of answering all the questionnaires. They will also be told that if they get tired, they can stop answering them and resume at another time of the day or on subsequent days. The fact that the trial is to be conducted in a real clinical setting with its possible errors and setbacks is also a limitation. Although standard operating procedures will be enforced, unexpected workflow disruptions could affect intervention fidelity. We are also aware that having the study subjects perform the IMT at home is not the best option even though we have provided all the necessary means (adequate instruction and performance record sheet) to make it as similar as possible to having it performed in the hospital (which is not possible due to organizational circumstances of the CRU). Because adherence relies on self-reported diaries and lacks electronic dose counters, compliance bias cannot be ruled out. No long-term follow-up beyond the 16 intervention sessions program means the durability of any observed benefits remains unknown.

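### With one baseline and one post-intervention value, the mixed-ANOVA interaction is a change-score t-test; ANCOVA on the baseline already collected is usually more precise and needs no extra data

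*Protocol article*

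**What the plan says.** The Statistical analysis section names one between-group model: "A mixed-design analysis of variance (ANOVA) will be performed to assess differential changes between groups over time". The test of interest is the group × time interaction, and the Abstract repeats the model. No baseline-adjusted model is named anywhere in the article.

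The measurement schedule has two points. The Abstract says "Outcomes will be collected at baseline and post-intervention", and the Clinical outcomes section, which covers ergometry, says "Before and after the intervention, the following assessments and evaluations will be performed". The Data collection section places ergometry before inclusion and again at the end of the programme, so a baseline MET value should exist for each randomised patient. Nothing is measured later: "No long-term follow-up beyond the 16 intervention sessions program means the durability of any observed benefits remains unknown".

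Only one outcome has a mid-programme value, and it serves a different purpose: "MIP will be reassessed midway through the program (at the end of week 4) to readjust the training load". That is maximal inspiratory pressure, a secondary outcome.

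The Sample size calculation section gives 33 per group, raised to 36, "considering a confidence level of 95% and a power of 80% in all cases". It states no SD and no baseline-to-post correlation. The Allocation concealment section describes simple 1:1 randomisation, with no stratification.

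**The concern.** A mixed ANOVA looks like a longitudinal model, but with two time points it reduces to comparing mean change between arms. Subtracting the whole baseline value is the most precise adjustment only if the regression slope of post on baseline is 1. When the slope is below 1, the change score over-corrects and carries baseline noise into the comparison.

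The stake is precision, together with how far a chance baseline difference moves the estimate. With 72 patients and no stratification, such differences are not rare, and the plan describes baseline comparability without adjusting for it by regression. The baseline value is already collected, so the lost precision can be recovered without recruiting or measuring anyone further.

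**Working it through.** **1. The plan's own figure.** At two-sided 5% and 80% power, the normal formula n = 2(1.96 + 0.84)²/d² with n = 33 gives d = 0.69; the t-based calculation gives d = 0.70. The stated 33 per group therefore fits an SD of about 3.5/0.70 = 5.0 for a difference of 3.5 ml O₂/kg/min, or about 2.18/0.70 = 3.1 for a difference of 2.18. The protocol gives no SD, so 33 can be back-solved but not reproduced. Two-sidedness is also an assumption.

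**2. Equivalence.** Let D = post − baseline for each patient. The interaction contrast is mean(D, IMT) − mean(D, sham), and its error term is the pooled within-arm variance of D. Hence F(1, 2n−2) = t². In one simulated dataset with 33 per arm, F(1,64) = 4.0531 and t² = 4.0531, both with p = 0.0483.

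**3. Variance with equal SDs.** Let s be the common SD at baseline and post (an assumption) and rho their correlation (also an assumption).

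- Change score, per-patient variance: 2s²(1 − rho)
- ANCOVA, residual variance: s²(1 − rho²)
- Ratio: (1 − rho²) / [2(1 − rho)] = (1 + rho)/2

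**4. Power at 33 per arm if the planned test has exactly 80%.** Divide the noncentrality at d = 0.70 by the square root of the ratio. The n per arm for 80% is 33 × ratio, rounded up (approximate).

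| rho | variance ratio | ANCOVA power | n per arm for 80% |
|---|---|---|---|
| 0.5 | 0.75 | 90% | 25 |
| 0.7 | 0.85 | 86% | 29 |
| 0.8 | 0.90 | 84% | 30 |
| 0.9 | 0.95 | 82% | 32 |

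**5. Check at this sample size.** Simulation with 20,000 runs and 33 per arm:

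| rho | variance ratio | power, change score | power, ANCOVA |
|---|---|---|---|
| 0.5 | 0.77 | 80.5% | 89.5% |
| 0.7 | 0.87 | 79.7% | 85.3% |
| 0.8 | 0.92 | 80.3% | 83.5% |

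The ratios lie slightly above theory because the slope has to be estimated. Residual degrees of freedom fall from 64 to 63. The ANCOVA estimate showed no bias beyond simulation error.

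**6. Unequal SDs.** Let k = post SD / baseline SD. The ratio becomes k²(1 − rho²) / (1 + k² − 2·rho·k). At k = 1.25:

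- rho 0.7: 1.5625 × 0.51 / (2.5625 − 1.75) = 0.797/0.8125 = 0.98
- rho 0.8: 1.5625 × 0.36 / (2.5625 − 2.00) = 0.5625/0.5625 = 1.00

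The tie at rho 0.8 arises because the slope rho × k is then exactly 1. In large samples the ratio never exceeds 1.

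**7. Chance imbalance.** With 36 per arm, the standard error of the baseline difference is √(2/36) = 0.236 SD. A difference above 0.25 SD in either direction corresponds to |z| > 0.25/0.236 = 1.06, which happens in about 29% of such trials.

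**The case against.** The strongest reply is that nothing here is invalid. The change-score comparison is unbiased under randomisation, and the Statistical analysis section contradicts no other part of the protocol. That stands: this is a matter of efficiency and of conditional balance.

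A second reply is that the gain may be small, and that too stands. At rho 0.9 it is 5% of variance, and with a post SD 1.25 times the baseline SD it is 2% or nothing at rho 0.7 to 0.8. At this sample size, estimating the slope also takes back a small part of the gain.

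A reader might infer three stronger things that the documents do not support:

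- **The trial is already short of its stated power.** With no SD given, 33 per group is consistent with about 80% power for a difference of 3.5 with SD about 5, or 2.18 with SD about 3.1. A shortfall appears only under particular assumed values.
- **Regression to the mean biases the planned test.** In a randomised comparison it affects both arms equally in expectation.
- **The mixed ANOVA gives no effect estimate.** With two time points the interaction is a difference in mean change, and the plan sets "significance level will be set at 5% with 95% confidence intervals". ANCOVA changes the precision of the estimate, not whether one exists.

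A separate analysis plan may exist. The point still applies, because the article fixes the model in both the Abstract and the Statistical analysis section.

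**Conclusion.** The point holds as an efficiency recommendation. For METs, the planned interaction test is exactly a change-score t-test; ANCOVA on baseline is no less efficient in large samples and adjusts for chance imbalance.

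If baseline and post SDs are equal, the variance reduction is 25%, 15%, 10% and 5% at rho 0.5, 0.7, 0.8 and 0.9. Against a planned test with 80% power, that is a gain of about 10, 6, 4 and 2 percentage points. Both rho and the SDs are assumptions, so the gain may be anything from worthwhile to negligible. The equivalence itself needs no assumption beyond the two-point schedule. The week-4 inspiratory pressure value does not affect it for METs.

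**What to change.** In the Abstract and the Statistical analysis section, replace the mixed ANOVA with:

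> Post-intervention METs will be compared between arms by ANCOVA with baseline METs as covariate; the adjusted mean difference with two-sided 95% CI is the primary result.

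Analyse each continuous secondary outcome in the same way, using its own baseline value as covariate. Do not add sex to a model meant for every outcome: the two sexual-function questionnaires are each given to one sex only, so a sex coefficient could not be estimated there.

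The statistical cost is one residual degree of freedom, with no new data and no further patients. The administrative cost is more than a sentence: the trial is registered and recruiting, so the change needs a dated amendment, made before anyone sees outcome data by arm.

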#### Plan for detecting adverse effects and procedure to be followed.

During the entire procedure, all incidents, whether cardiological events or not, will be monitored and recorded. They will be analyzed by the researcher in charge of the study at the hospital and by the principal investigator, and if they are attributable to the intervention, the corresponding measures will be taken.

### Ethics

The present project will follow the ethical principles established for medical research on human subjects, according to the Declaration of Helsinki. The present clinical trial was approved by the Provincial Research Ethics Committee of Malaga (Spain) with Code SICEIA-2024–001869 in session number 9, held on 09/26/2024. Since data from real subjects will be used, it is essential to guarantee their confidentiality, privacy, and data protection. To this end, the participation of the subjects will be voluntary, and it will be an indispensable requirement to sign a written informed consent form for participation in the study. Participants will be able to withdraw from the study whenever they wish to do so. To safeguard the identity of the participants, their names and surnames will be coded in the database. This is a low-intervention clinical trial, since IMT is a very safe intervention, as it is routinely performed in other populations of chronic cardiac and respiratory patients without any relevant adverse effects having been reported. In addition, patients will be scrupulously stratified according to their cardiovascular risk, and the CRU at HUVV has extensive experience in training this type of patient, and its professionals are in constant training. The damages incurred by the participants will be covered by individual or collective self-insurance that the researcher in question has already contracted for the usual practice of his or her profession.

To publish the results of the project in international peer-reviewed journals and present the results at congresses worldwide, the Consolidated Standards of Reporting Trials (CONSORT) statement will be followed. In addition, as part of the knowledge translation strategy, we will disseminate the results on institutional websites and social media, contact news organizations, and identify partner institutions interested in the results. It is not planned to use professional scientific writers because the scientific articles will be written by the researchers of the study.

## Discussion

The present study will analyze the effect of adding IMT to a CRP in people with AMI who underwent revascularization by PCI. It is expected that CF and MIP will improve because there is some evidence (low and moderate) of this, as concluded in a recent review with meta-analysis by Fabero-Garrido et al. [16]. Furthermore, in similar clinical populations such as patients with HF, there is a high level of evidence that these outcomes and QoL, improve [18]. Therefore, it can be expected that the results are similar in AMI, in spite of no improvements in QoL have been evidenced yet in PCI patients. Nor have significant gains in sleep quality been observed to date, according to the available studies. In those variables without prior evidence, such as peripheral muscle strength, social support, anxiety, depression, coping with the disease, sexual dysfunction, eating habits, and body composition, we hypothesize that there will be an improvement, since increasing CF will reduce dyspnea during daily activities and thus could contribute, in our opinion, to the enhancement of other aspects of the individual. We decided to perform IMT at 70% of MIP based on a recent meta-analysis by Azambuja et al. [18]. As they concluded, training at loads above 60% of MIP had greater increases in inspiratory muscle strength, CF, and QoL in patients with HF. We expect these greater effects to occur in people with AMI as well. In the case of CF, our main outcome, the improvement occurs for three reasons. First, early inspiratory muscle fatigue is delayed because it induces metaboloreflex which decreases blood flow to the peripheral musculature [43–46]. Second, blood supply to the peripheral musculature is increased by decreasing the blood demand of the inspiratory musculature [47–49]. Thirdly, IMT can reduce the peripheral chemoreflex response and enhance heart function. This is directly linked to decreased sympathetic activity in individuals with HF, leading to better systemic vasodilation, improved blood flow to peripheral muscles, greater ventilatory efficiency, and, as a result, increased CF [50]. Although undertaking a CRP itself improves psychosocial outcomes, dedicated IMT has further reduced fatigue, depression and perceived dyspnoea in patients with stable angina [51] and HF [52]. IMT has also demonstrated improvements in the psychosocial domain in healthy people [53] and people with chronic obstructive pulmonary disease [54,55]. Improved breathing efficiency may decrease the cognitive load associated with exertional breathlessness, fostering greater self-efficacy, exercise adherence and ultimately enhanced QoL. Women remain under-represented in cardiac rehabilitation (CR) trials, and it is a relevant aspect for the individualization of a CRP [56]. From a physiological perspective, women have lower respiratory muscle mass and lower basal MIP than men [57], which may predispose them to relatively greater improvements after IMT. Emerging evidence suggested that female patients obtain smaller absolute but similar relative gains from a CRP [58]. Therefore, our results will allow us to explore effect modification by sex, which may inform personalized prescriptions and help close the persistent gender gap in CR outcomes.
